# IDC-IMPROVE: protocol for a cluster randomised feasibility trial of a care bundle to improve indwelling catheter care (IDC) in residential aged care homes in Australia

**DOI:** 10.1186/s40814-025-01700-x

**Published:** 2025-10-17

## Abstract

**Background:**

Indwelling urinary catheters (IDCs) are used by approximately 8% of Australian aged care residents. IDC use is often warranted but entails numerous risks, particularly if used longterm. Risks include catheter-associated urinary tract infections, catheter blockage, catheter leakage, bladder spasm, pain, urethral trauma and haematuria, and increased risk of hospitalisation. The Royal Commission into Aged Care Quality and Safety identified poor quality, unsafe practices related to IDCs in aged care homes. Enhancing the knowledge, confidence, and skills of aged care staff to deliver catheter care for residents with IDCs is fundamentally important. The IDC-IMPROVE project is supporting aged care providers to meet the care needs of people with IDCs in Australian aged care homes, by designing and validating a suite of resources titled the IDC-IMPROVE Catheter Care Bundle.

**Aims:**

This study aims to establish the feasibility of conducting a definitive randomised control trial to evaluate the effects of the IDC-IMPROVE Catheter Care Bundle in aged care homes in Australia.

**Method:**

A multi-centre, facility-level clustered randomised control (cRCT) feasibility trial in 24 aged care homes across Victoria, Queensland, and South Australia. Twelve homes will receive the intervention and 12 will continue usual care. The IDC-IMPROVE Catheter Care Bundle intervention comprises principles for person-centred catheter care, online training for nurses and personal care workers, a practical skills workshop for nurses, a toolkit for managers, and an evidence-to-practice support model. The feasibility of the intervention will be assessed through a mix of qualitative and quantitative methods, including surveys, interviews, and audits. Feasibility outcomes are: (i) The acceptability of the Bundle, (ii) The fidelity of the implementation, (iii) The compatibility of the Bundle with standard aged care home IDC care.

**Discussion:**

By enhancing the knowledge, confidence and skills of the aged care workforce, IDCIMPROVE aims to reduce IDC-related complications. This study will provide insights into the acceptability and implementation of the intervention, informing future large-scale trials and potential policy changes.

**Ethics:**

The study has been approved by Austin Health Human Research Ethics Committee (reg: HREC/107165/Austin-2024) and is registered on the Australian New Zealand Clinical Trials Registry (reg: ACTRN12624001178538p).

**Supplementary Information:**

The online version contains supplementary material available at 10.1186/s40814-025-01700-x.

## Background

Indwelling urinary catheters (IDCs) are devices inserted into the bladder via the urethra or lower abdomen (suprapubic region) and remain in place to aid urine drainage. International estimates suggest between 5 and 8% of people in long-term care homes have an IDC [1–3]. During 2022–2023, 8.4% (15,249) of people receiving government subsidised residential aged care in Australia required some form of catheter care [4].^1^

Although potentially beneficial, IDC use is associated with higher risks of morbidity [5, 6]. IDCs provide a mechanism for bacteria to enter the bladder and therefore people with an IDC are at risk of developing a catheter-associated urinary tract infection (CAUTI). The longer a catheter remains in place, the higher the risk. The European Association of Urological Nurses (EAUN) defines long-term catheterisation as the use of a catheter remaining in situ for ≥ 14 days [7]. CAUTIs can lead to other complications such as encrustation and catheter blockage [8], for which treatment is challenging [9]. CAUTIs and catheter blockages are serious events that may result in presentation to emergency departments [10]. Transferring older people from aged care homes to emergency departments or hospital admission has been associated with further risks, including delirium, increased functional decline, nosocomial infections, and pressure injuries [11, 12].

Projections from the Australian Institute of Health and Welfare (AIHW) and Australian Bureau of Statistics (ABS) show that Australia’s population over 65 will continue to grow substantially over the coming decades, driven by increased life expectancy and lower birth rates [13]. By 2066, it is estimated that around 23% of the population will be over 65. As this demographic shift progresses, age-related health issues—including conditions that may necessitate long-term use of medical devices like IDCs—are expected to rise due to increased healthcare demands among older individuals.

This trend will likely impact the aged care sector, as a significant portion of the older population transition into aged care homes. In these settings, residents often have complex health needs requiring specialised care and skilled staff, particularly for indwelling catheter management and other chronic care interventions. Meeting this demand will necessitate upskilling the workforce through education and training in IDC care and related areas to provide appropriate support and prevent complications associated with long-term use.

The day-to-day care of people with IDCs in aged care homes in Australia is undertaken by personal care workers (PCWs) and registered and enrolled nurses. This workforce is central to the quality and safety of care in residential aged care homes. The Australian Royal Commission into Aged Care Quality and Safety heard evidence of poor quality, unsafe practices related to IDCs and called for interventions to strengthen the capacity of this workforce to care for older Australians [14].

Through the *Improving indwelling urinary catheter care in residential aged care* (IDC-IMPROVE) project, we aim to improve knowledge and skills in catheter care among the residential aged care workforce. Specifically, we aim to support nurses to perform routine uncomplicated catheter exchanges on site; identify, prevent and manage IDC-related problems; and recognise and address the inappropriate use of an IDC.

We have designed and validated a comprehensive, evidence-based intervention titled the *IDC-IMPROVE Catheter Care Bundle* (hereafter referred to as the *Bundle*). The *Bundle* was developed in consultation with key stakeholders and with reference to the most recent comprehensive evidence-based guidelines from the EAUN [7] about urinary catheter management. It has been adapted to suit residential aged care nursing and care staff. The *Bundle* consists of the following:Principles for person-centred catheter careAn online course for registered and enrolled nurses about person-centred IDC careAn online course for PCWs about person-centred IDC care.A catheter care toolkit for managers/senior leaders.

We have also partnered with Continence Health Australia (CHA) to deliver site-based Catheterisation Skills Workshops, where nurses who have completed the online course can develop and practice the skill of inserting and changing IDCs in a safe environment. This article presents the protocol for the next part of the project, a cluster randomised feasibility study of the *Bundle* in residential aged care homes.

This is the first time a trial of a catheter care bundle has been conducted in residential aged care homes in Australia. Investigating feasibility will support refinement of the intervention and the outcome measures for this setting. Moreover, recent research has identified several barriers that impede the involvement of residential aged care homes in research, including staff shortages, systemic and regulatory pressures, under-resourcing, and difficulties selecting unbiased samples [15, 16]. The Australian Royal Commission into Aged Care Quality and Safety recommended increasing the research capacity of Australia’s aged care sector to support system reforms and ongoing quality improvement [14]. It is therefore appropriate and ethical to investigate feasibility via a smaller scale trial before conducting a definitive clinical trial where there are significant risks of failure [17]. The cluster randomised feasibility trial is being conducted in accordance with the extended CONSORT guidelines for feasibility studies [18]. We will use a mixed methods approach with qualitative and quantitative components to determine feasibility.

## Methods

The aims of this study are to determine the feasibility of implementing the *Bundle* in residential aged care homes and to determine the utility and feasibility of a definitive phase III trial to assess its effectiveness. The aims are encompassed by the following five objectives:To determine the acceptability of the *Bundle* to end users in residential aged care homes.To explore the fidelity of the implementation of the *Bundle*.To investigate the compatibility of the *Bundle* with current catheter care practices, procedures and policies.To investigate the internal consistency, construct validity and convergent validity of a scale developed to measure nurses’ knowledge and confidence to provide person-centred IDC care.To gather descriptive pilot data related to rates of IDC-related complications, and staff knowledge and confidence to provide person-centred IDC care.

### Feasibility cRCT

This is a multi-centre, facility-level cluster randomised control feasibility trial with an embedded process evaluation conducted in residential aged care homes in Australia. After baseline data are collected for all outcome measures, 12 aged care homes will be randomised to receive the intervention and 12 will continue to provide usual practice (control). Each cluster comprises one site (residential aged care home). The control sites are included to assess acceptability of randomisation and fidelity to data collection and to provide a comparator for pilot data. Control sites will receive some elements of the *Bundle* after the trial closes and data collection is completed at their site. Figure 1 provides an overview of the trial.

**Fig. 1 Fig1:**
[figure not shown]
Flow diagram illustrating cluster and participant progression through the NARI IDC-IMPROVE feasibility randomised controlled trial

### Setting

The trial will be conducted over approximately 6 months in 24 aged care homes across three Australian states: Victoria, Queensland, and South Australia. Residential aged care homes provide accommodation and 24-h personal care for older people (aged 65 + years) who can no longer live in their own home [19, 20]. Most aged care in Australia is subsidized and regulated by the Commonwealth government and includes nursing and other general healthcare, but not acute or sub-acute medical care, which falls under state and territory jurisdictions.

The number of sites allows for a diverse sample that reflects the profile of the residential aged care sector in each state. During recruitment, homes will be stratified according to three sizes (small, 60 or fewer residents; medium, 61–100 residents; large, 101 + residents) to ensure a representative sample. We will aim to recruit a diverse sample regarding other site characteristics (e.g. ownership structure, location). In a larger future trial, formally stratifying for these characteristics will be considered.

### Site inclusion/exclusion criteria

The inclusion criteria for sites are the following: (a) an approved residential aged care provider in Victoria, Queensland, or South Australia, (b) has at least 4 nursing staff employed who are available to participate in the study for trial period, and (c) one or more resident with an IDC at time of enrolment. The exclusion criteria are the following: (a) the home is for sale (the potential individual site), (b) does not have a resident with IDC use at the time of enrolment.

### Population

The intervention is multifaceted and targets different residential aged care staff groups, comprising managers/senior leaders, nurses (both Registered (RN) and Enrolled (EN)), and PCWs. This is intended to facilitate multi-level practice change including organisational policy, clinical care, and personal care. All participants must be over 18 years old.

### Participant inclusion/exclusion criteria

#### Nurses

We aim to recruit at least four nurses (RNs and ENs) per site (96 total), as the face-to-face component of the training will be delivered to groups of four. Inclusion criteria require participants to be employed at an enrolled site (permanent or casual); registered to practice in Australia as an EN or RN with the Nursing and Midwifery Board of Australia; are planning to remain employed at the site for the trial period. Exclusion criteria are as follows: the nurse cannot commit to completing the online course about person-centred IDC care and/or attend the Catheterisation Skills Workshops.

#### Personal care workers

We aim to recruit 100 PCWs across intervention and control sites. Inclusion criterion is that the participant plans to be employed at the site during the trial period.

#### Managers and senior leaders

We aim to recruit 1–2 managers or senior leaders from each intervention and control site. To participate, they must have responsibilities in managing or coordinating the overall quality of care (e.g. infection control, staff development) and anticipated to remain employed at the site during the trial period.

#### Residents

All residents at participating sites who have IDCs and are capable of providing informed consent, or whose proxy can provide consent, will be invited to participate. Residents will not be receiving any treatment or completing any measures. Consent is being sought for permission to extract data from residents’ medical records.

### Sample size calculation

A sample size calculation was conducted to estimate the number of participants (nurses) required. Assuming a desired trial completion rate of 80% (*p* = 0.80) (see Table 3) and a maximum likely error of 10% with a 95% confidence level (*α* = 0.05), a required sample of 62 nurses was determined. This calculation was performed using R software. Our target sample size of 96 nurses accommodates the possibility of variations in cluster size, resulting from the availability of nursing staff at different sites.

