**Table 2 Tab2:**
[figure not shown]
Timeline of study procedures, including enrolment, interventions, and assessment points

**Table 3 Tab3:** Criteria, data collection methods, and thresholds for progression to a definitive trial

Criteria	Data collection	Threshold
(ii) Acceptability of the bundle	• Feedback surveys • Audit tool • Qualitative interviews	• 75% + participants “satisfied” or “very satisfied” • Thematic analysis of qualitative interviews • Descriptive analysis of audit tool
(iii) Fidelity of implementation	• Participant completion and withdrawal record • KCS-Nurse • KCS-PCW • NPC-Scale-SF • Clinical data extraction form	• Site retention: 20 sites complete all trial phases • Participant retention: ≥ 80% of enrolled participants complete all study follow-ups (t_0_, t_1_, t_2_) • Fidelity to data collection: 75% of all *expected* data points collected across KCS-Nurse, KCS-PCW, NPC-Scale-SF, and Clinical Data Extraction Forms from sites and participants who complete all trial phases • Internal Consistency of KCS-Nurse: Achieves acceptable internal consistency
(iv) Compatibility of bundle with standard practice	• Qualitative interviews • Audit tool	• Thematic analysis of qualitative interviews • Descriptive analysis of audit tool

Prior to site randomisation, information will be collected from organisations on their size, ownership and staffing, and from individual nurses and PCWs in terms of their qualifications, years in nursing and in working in residential aged care. The research team will provide sites with extraction forms to obtain key information from the medical records of residents with IDCs who consent to participate in the study. Research staff will be trained in obtaining informed consent and in the use of the extraction forms prior to inviting residents to participate. We anticipate some participating nurses may complete the online course but will be unable to complete a workshop due to workshop capacity limitations. These nurses will be flagged, and their outcome data will not be combined with workshop participants’ data.

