### Data analysis

Feasibility outcomes will be analyzed using quantitative and qualitative approaches. The R software program will be used for all quantitative data manipulation and analysis. Descriptive analysis will be conducted for all demographic and scaled outcomes, reporting at baseline (t_0_), post-intervention (t_1_), and follow-up (t_2_) timepoints. The KCS-Nurse scores will be assessed for normality using descriptive statistics and histograms. All subscale scores will be analysed using the median with the 25th and 75th percentiles (IQR), and normally distributed scores will be additionally analysed with means and 95% confidence intervals (CI). Discrete and categorical data will be analysed using frequencies with relative frequencies. Descriptive analyses will be assessed according to progression criteria and reported against the prescribed thresholds in Table 3.

Survey feedback will be summarised. Qualitative interview data will be recorded, transcribed verbatim, checked for accuracy, and analysed using thematic analysis [21]. Two members of the research team will analyse the data independently and conduct a thematic analysis. Qualitative findings will be used alongside the analysis of progression criteria and feedback from surveys to conduct a process evaluation. This will explore how the intervention was experienced by participants and any changes that they think would improve the trial and intervention and their implementation. A “Framework” analytical approach [22] informed by the 14-domain version of the Theoretical Domains Framework [23] and based on the research objectives will be used to describe the feasibility of the *Bundle*.

The internal consistency, construct validity and convergent validity of the KSC-Nurse will be analysed. Internal consistency will be estimated using Cronbach’s alpha. Construct validity will be estimated using confirmatory factor analysis (CFA), based on the 5 key competency domains of the scale. The model fit will be assessed using the Comparative Fit Index (CFI). Convergent validity will be estimated by calculating the Pearson correlation coefficient between the KSC-Nurse and the Nurse Professional Competence Scale-Short Form (NPC Scale-SF) [24], accounting for clustering. The intra-cluster coefficient (ICC) will be calculated based on KSC-Nurse scores to explore clustering effects and inform implementation of the instrument in other studies.

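### The 62-nurse requirement assumes independent nurses although homes are the clusters, so ±10 points is not delivered at 62 and is not assured at the target of 96

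*Protocol article*

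**What the plan says.** The Sample size calculation section takes a completion rate of 80%, pointing to Table 3, together with "a maximum likely error of 10% with a 95% confidence level", and concludes that "a required sample of 62 nurses was determined". It gives no ICC and no design effect. It then says: "Our target sample size of 96 nurses accommodates the possibility of variations in cluster size", and attributes that variation to how many nurses each site can make available.

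The Feasibility cRCT section fixes the cluster: "Each cluster comprises one site (residential aged care home". There are 24 homes, 12 per arm. The Nurses section sets recruitment: "We aim to recruit at least four nurses (RNs and ENs) per site (96 total", which is 24 × 4.

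Table 3 sets two retention criteria. One is that at least 80% of enrolled participants complete all follow-ups. The other is "Site retention: 20 sites complete all trial phases", which leaves room for four of the 24 homes to drop out.

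**The concern.** A precision calculation for a proportion needs an allowance for within-cluster correlation when people are recruited in groups and the outcome can be shared within the group. Trial completion is such an outcome: if a home withdraws, all of its nurses become non-completers together. Table 3 shows that the authors foresee homes leaving. The protocol's only formal sample size calculation makes no such allowance, and the reason given for going from 62 to 96 is a different one.

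At stake is how firmly the observed completion rate can inform planning of a definitive trial. A reader would take ±10 points as guaranteed at 62 and comfortably exceeded at 96. Neither follows from the document. Because 62 is presented as the requirement, it also reads as an acceptable floor if nurse availability falls short.

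**Working it through.** **Inputs from the protocol article.** p = 0.80, d = 0.10, 95% confidence (z = 1.96), stated n = 62, target 96, 24 homes, 4 nurses per home. **Assumed, because the document gives none:** the ICC for completion (0.05 to 0.30) and, in one check, a coefficient of variation (CV) of cluster size of 0.5.

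**1. Reproduce 62.** n = z²p(1−p)/d² = 1.96² × 0.8 × 0.2 / 0.10² = 61.46, rounded up to 62. The match is exact with a design effect of 1, so no clustering allowance is hidden in the figure.

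**2. Half-width with clustering.** DE = 1 + (m − 1) × ICC, and half-width = 1.96 × √(0.16 × DE / n). For 62 nurses over 24 homes, m = 62/24 = 2.58. For 96 nurses, m = 4.

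| ICC (assumed) | Half-width at 62 (points) | Half-width at 96 (points) | Nurses needed for ±10 at 4 per home |
|---|---|---|---|
| 0 | 9.96 | 8.0 | 62 |
| 0.05 | 10.3 | 8.6 | 71 |
| 0.10 | 10.7 | 9.1 | 80 |
| 0.20 | 11.4 | 10.1 | 99 |
| 0.30 | 12.1 | 11.0 | 117 |

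**3. ICC at which ±10 points is just met.**
- At 62: (62/61.46 − 1)/1.58 ≈ 0.006.
- At 96, equal clusters: (96/61.46 − 1)/3 = 0.187.
- At 96, unequal clusters with DE = 1 + ((1 + CV²)m − 1) × ICC and CV = 0.5: (96/61.46 − 1)/4 = 0.14.

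The reason the protocol gives for the margin, uneven cluster sizes, thus itself uses up part of that margin once any correlation exists.

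**4. Loss of whole homes (illustrative).** Hold overall completion at 80%, with four nurses per home and equal retention in the remaining homes. If a fraction f of homes is lost, the between-home variance is 0.64f/(1 − f). Dividing by 0.16 gives ICC = 4f/(1 − f).
- One home lost: ICC 4/23 = 0.17, half-width 9.9 points at 96.
- Two homes lost: ICC 8/22 = 0.36, half-width 11.6 points.
- Four homes lost: the other 20 retain 0.80 × 24/20 = 0.96. The variance is (20/24)(0.16²) + (4/24)(0.80²) = 0.128, so ICC = 0.128/0.16 = 0.80. Then DE = 1 + 3 × 0.80 = 3.4, effective n = 96/3.4 = 28.2, and half-width = 14.8 points.

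The four-home case is a boundary, not a forecast.

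**The case against.** The strongest reply is that the trial recruits 96 nurses, not 62, and that 96 keeps the half-width within 10 points up to an ICC of about 0.19. At 0.20 the excess is only 0.1 point. Four is also a minimum per site, the analysis is descriptive, and the authors recognise clustering: the Data analysis section allows for it in the convergent-validity correlation and plans an ICC from KCS-Nurse scores. Most of this stands, and it limits the point to one of justification and reporting. It does not rescue 62 as a requirement. An ICC for knowledge and confidence scores also says little about the ICC for completion.

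Four stronger readings are tempting, and the document does not support them.
- A reader might infer that the planned score intervals ignore clustering, because "normally distributed scores will be additionally analysed with means and 95% confidence intervals (CI" carries no mention of it. The section names no variance method, and that detail may sit in an analysis plan that is not shown.
- A reader might infer that progression decisions would be falsely certain. The quantitative retention, satisfaction and data-collection criteria in Table 3 are point thresholds with no interval attached, so a wider interval would not change whether they are met.
- A reader might infer that the plan's tolerances imply an ICC of 0.80. The two retention criteria are separate minimum standards. Having both fall exactly on their limits, with all four lost homes contributing no completers, is a constructed extreme.
- A reader might infer that 96 is too few. Nothing in the document places the ICC for completion above 0.19.

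**Conclusion.** The point holds for the sample size statement. The 62 is correct arithmetic for independent nurses, but it does not fit a design in which nurses are grouped by home. Its margin is 0.04 points under independence (9.96 against 10) and disappears above an ICC of about 0.006. At 96 the stated precision is met up to an ICC of about 0.19 with equal clusters, or about 0.14 with a cluster-size CV of 0.5, and is missed beyond that. In the whole-home-loss illustration at 80% overall completion, one lost home stays just inside 10 points, two give 11.6 and four give about 15.

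All ICC and CV values are assumptions, and the half-widths use the normal approximation and the usual design-effect formula. The consequence is an overstated precision for a rate that informs progression. It is not an invalid trial or a wrong decision rule. The correction is worth making, but it is of moderate importance.

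**What to change.** Keep the recruitment target of 96 and revise the Sample size calculation section as follows.
- State that 62 applies only if nurses' completion is independent within homes.
- Replace the ±10-point claim with the design effect and half-width for 24 homes × 4 nurses over a stated ICC range. For example, ICC 0.05, 0.10, 0.20 and 0.30 give design effects 1.15, 1.30, 1.60 and 1.90 and half-widths 8.6, 9.1, 10.1 and 11.0 points. Note the effect of unequal cluster sizes.
- Add a sensitivity case for the loss of whole homes, labelled as illustrative.
- State that the completion rate will be reported with a 95% CI that allows for clustering by home, for instance from site-level summaries or from GEE with a small-sample correction.

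The cost is a few sentences, one standard analysis step and a less favourable stated precision. No extra homes or nurses are needed, and the Table 3 thresholds can stay as they are.
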